# A prospective, randomised, controlled, double-blind phase I-II clinical trial on the safety of A-Part^® ^Gel as adhesion prophylaxis after major abdominal surgery versus non-treated group

**DOI:** 10.1186/1471-2482-10-20

**Published:** 2010-07-06

## Abstract

**Background:**

Postoperative adhesions occur when fibrous strands of internal scar tissue bind anatomical structures to one another. The most common cause of intra-abdominal adhesions is previous intra-abdominal surgical intervention. Up to 74% of intestinal obstructions are caused by post surgical adhesions. Although a variety of methods and agents have been investigated to prevent post surgical adhesions, the problem of peritoneal adhesions remains largely unsolved. Materials serving as an adhesion barrier are much needed.

**Methods/Design:**

This is a prospective, randomised, controlled, patient blinded and observer blinded, single centre phase I-II trial, which evaluates the safety of A-Part^® ^Gel as an adhesion prophylaxis after major abdominal wall surgery, in comparison to an untreated control group. 60 patients undergoing an elective median laparotomy without prior abdominal surgery are randomly allocated into two groups of a 1:1- ratio. Safety parameter and primary endpoint of the study is the occurrence of wound healing impairment or peritonitis within 28 (+10) days after surgery. The frequency of anastomotic leakage within 28 days after operation, occurrence of adverse and serious adverse events during hospital stay up to 3 months and the rate of adhesions along the scar within 3 months are defined as secondary endpoints. After hospital discharge the investigator will examine the enrolled patients at 28 (+10) days and 3 months (±14 days) after surgery.

**Discussion:**

This trial aims to assess, whether the intra-peritoneal application of A-Part^® ^Gel is safe and efficacious in the prevention of post-surgical adhesions after median laparotomy, in comparison to untreated controls.

**Trial registration:**

NCT00646412

## Background

Post surgical adhesions are quite common, i.e. they can affect up to 93% of patients undergoing abdominal surgery [1,2]. Adhesions are internal scars developing after trauma and involving the injured tissue and the peritoneum [3]. The magnitude of the problems caused by adhesions was highlighted by several studies [4-7]. Depending on the location and the structure of the adhesion serious complications may be caused thereby, such as large and small bowel obstruction. Pelvic adhesions are associated with infertility in 15-20% of cases [8]. A number of products that help to reduce or to prevent tissue adhesion are marketed [2]. Barrier materials in various forms such as films, viscous gels and intra-peritoneal solutions have been used clinically for the prevention of surgical adhesions. However, these materials have had limited success, and no treatment is adopted so far as a standard therapy [9].

### Rationale

Several materials and methods have been tested for the prevention of post surgical adhesions, but the problem is still unsolved [10-12]. The most established method in adhesion prevention is to apply a barrier between the wounded surfaces. Barrier materials should be easy to apply and should remain in place for several days to allow serosal re-epithalization and should be resorbed afterwards and excreted without systemic reactions or inappropriate accumulation. Materials should be non-inflammatory and non-reactive and should not interfere with the healing processes of sutures, anastomoses or the incision.

### Purpose

A-Part^® ^Gel [13] a bioresorbable transparent gel composed of polyvinylalcohol (PVA) and carboxymethylcellulose (CMC) was developed to meet these features mentioned above. Both components PVA and CMC are already used for various biomedical applications [14-17]. The established use of PVA and CMC has confirmed their good biocompatibility [10,18-25]. Material characteristics and preclinical data of animal studies have established the promising properties of A-Part^® ^Gel as a new measure against post surgical adhesions [26,27]. Therefore this prospective, randomised, controlled, patient and observer blinded trial was designed as a first evaluation of the safety of A-Part^® ^Gel as an adhesion prophylaxis after abdominal surgery in comparison to a non treated control group in man.

## Methods/Design

### Objectives of the study

The aim of this study is a first assessment of the safety of A-Part^® ^Gel applied as an adhesion prophylaxis after major abdominal surgery, by specific observation of two major complications of abdominal surgery; wound healing impairment or peritonitis; in comparison to a non treated control group (primary objective) within 28 (+10) days after surgery (for definition see table 1). The incidence of adverse events and serious adverse events occurring 3 months postoperatively, with special attention to anastomotic leakage, between the two treatment groups, will be used to further consider the safety of A-Part^® ^Gel. To explore the efficacy of A-Part^® ^Gel in reducing post-surgical adhesions, ultrasound examination will be performed up to 3 months postoperatively (secondary objectives).

**Table 1 T1:** Diagnostic criteria of complications

Complication	Diagnostic criteria/Definition
**Impaired wound healing**	
a)Delayed wound healing	• Necrosis of wound edge
	• Dehiscence
	
b) Development of surgical site infection	• Purulent secretion from the wound
	• Germ organism isolated from an aseptically obtained culture of fluid or tissue from superficial incision
	• Local signs of infection or systemic signs (fever, leukocytosis, rising CRP) without other plausible causes (e.g. pneumonia, urinary tract infection)
	• Diagnosis of an abscess in deep soft tissue (an abscess in deep soft tissue is defined as microbiological verification of suspect specimen which is generally taken by means of ultrasonic puncture)
	
**Peritonitis**	• fever, leukocytosis, abdominal pain, muscular defense, absence of bowel sounds, metabolic disturbances or severe hypotension with multiple organ failure (MOF)
	Diagnosis confirmed by:
	▪ Fluid collection by puncture or drainage
	▪ Sonography
	▪ Computed tomography
	▪ Re-Intervention/Revision
	
**Anastomosis leakage**	• Fever, abdominal pain, metabolic disturbances, intra-abdominal abscesses, or sepsis with multiple organ failure (MOF)
	Diagnosis confirmed by:
	▪ Fluid collection by puncture or drainage
	▪ Sonography
	▪ Computed tomography
	▪ Colonic contrast enema (water soluble contrast medium)
	▪ Re-Intervention/Revision

The incidence of adhesions between the visceral organs and the abdominal wall will be diagnosed by ultrasound examination using a linear-array transducer. The scar of the abdominal incision will be divided into equal parts of 2,5 cm, starting 2 cm from the cranial beginning of the scar. At each assessment point spontaneous visceral slide (produced by regular and deep respiration motion) will be examined using ultrasound scanning. Reduced movement following respiration will count as restricted visceral slide, i.e. adhesions. The total number of assessment points and the number of assessment points with adhesions will be documented.

#### Primary endpoint

- Occurrence of wound healing impairment or postoperative peritonitis within 28 (+10) days after surgery.

Impaired wound healing is defined as delayed wound healing or the development of surgical site infection.

Delayed wound healing has to be diagnosed if at least one of the following criteria is fulfilled:

- Necroses of wound edges occur.

- Primary or secondary dehiscence occurs (primary dehiscence is defined as retreating of wound edges immediately after surgery; secondary dehiscence is defined as retreating of wound edges after start of the wound healing.

Surgical site infection and postoperative peritonitis has be assumed as present, if one or more of the criteria which are shown in table 1 are fulfilled.

#### Secondary endpoints

- Occurrence of anastomosis leakage within 28 (+10) days after surgery.

- Occurrence of Adverse Events (AE) and Serious Adverse Events (SAE) during the postoperative hospital stay and up to 3 months after surgery.

- Adhesion rates along the scar after 14 days, 28 (+10) days and 3 months (±14 days) days examined by ultrasound.

For the definition of anastomosis leakage please see table 1. Assessment of adhesion development will be done by ultrasound assessment. Sigel *et al. *described a technique for non-invasive ultrasound examination to detect and map abdominal adhesions. The findings that identify abdominal wall adhesions are based on the presence or restriction of ultrasonically observed movement of abdominal viscera in reference to abdominal wall.

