### Design

This is a prospective, randomised, controlled, double-blinded, single centre study. Patients will be blinded as well as the evaluating physician conducting the ultrasound examination. In case of a non sufficient recruitment this study can be expanded into a multicentre trial. Patients enrolled in the trial will be randomly allocated either to the treatment group receiving A-Part^® ^Gel or to the untreated control group (for inclusion and exclusion criteria see table 2). Randomisation will take place during the operation. Initially there will be a staggering of the treatment of the patients, so that during the early phase of the study there is a one-by one exposure of patients to A-Part^® ^Gel. Both groups consist of 30 patients. After discharge from the hospital the investigator will examine the patients at 28 days (+10) and after 3 months (±14 days) after surgery (figure 1).

**Table 2 T2:** Eligibility Criteria

Inclusion criteria	Exclusion criteria
• Patients of both sexes undergoing a primary elective median abdominal incision	• Patients with a known history of adhesion or peritonitis
• Age equal or greater than 18 years	• Patients with a known sensitivity to polyvinylalcohol or carboxy-methylcellulose
• Written informed consent	• Simultaneous participation in another clinical trial with interfering end-points
• Expected incison length ≥15 cm	• Emergency surgery
• Expected survival time more than 12 months	• Patients with peritoneal carcinosis or peritoneal dialysis
• For female adults of reproductive potential: negative pregnancy test at visit 1 and sufficient contraception from time of written consent up to at least 4 months	• Patients with systemic immunsuppression (e.g. hydrocortisone >50 mg per daily, other immunsuppressants like Azathropin, Mycophenolatmofetil, Ciclosporin, Everolimus, Methotrexat ect.), chemotherapy or radiotherapy within the last 2 weeks prior surgery
	• Patients with ascites >200 ml
	• ASA > 3
	• Patients with intra-abdominal abscess or other intra-abdominal infection
	• Renal impairment (Creatinine >1.3 mg/ml)
	• Pregnant or breast-feeding women
	• Lack of compliance
	• Surgical procedures or patients which require insertion more than 2 intra abdominal drains

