### Statistical consideration and sample size estimation

The aim of this study is a first assessment of the safety of the application of A-Part^® ^Gel as an adhesion prophylaxis after major abdominal surgery as compared to control. Sample size considerations are not based on statistical calculations, but on the feasibility of recruitment. It is planned to randomise 60 patients between A-Part^® ^Gel and control, because this is expected to be feasible within six months from a single centre. This phase I study is conducted as a first application of A-Part^® ^Gel in man, and its aim is to receive first safety data as compared to control. The power considerations are based on the specific observation of two major complications of abdominal surgery "occurrence of wound healing impairment or postoperative peritonitis within 28 (+10) days after surgery" as a primary combined endpoint. It is assumed that without application of the A-Part^® ^Gel wound healing impairment will occur with a probability of about 5-10% and postoperative peritonitis will occur with a probability of about 2-5% [31-33]. This leads to the assumption that the combined endpoint will occur in the control group with a probability of about 10-15%. It is the aim of the study to show that the application of A-Part^® ^Gel does not lead to an unacceptable increase in the probability of occurrence of the combined endpoint i.e the non-inferiority of A-Part Gel^® ^as compared to the control. Under the assumption that the application of A-Part^® ^Gel does not increase the probability of the combined endpoint, this study can show at one-sided significance level α = 5% with a power of 80% that the absolute difference of the event probabilities between both treatment groups is not larger than 20-25% [34].

The two-sided 90%-confidence interval for the absolute difference (A-Part^® ^Gel minus control) of probability of occurrence of the primary endpoint will be calculated. If the upper bound of this confidence interval is below 0.25, the hypothesis that the difference is 0.25 or larger will be rejected. Adverse event incidences, wound healing impairment, postoperative peritonitis, adhesion and complication rates will be calculated with two-sided 90% confidence intervals.

The safety analyses will be conducted in the safety population, including all randomized patients with group assignment by treatment received. All analyses will be done with the Statistical Analysis System (SAS).

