Oxidized regenerated cellulose (ORC) is another barrier used for the prevention of adhesions [42]. When applied to raw peritoneal surface, it gels within 8 h [43]. Experimental and clinical models reported good preventive results by forming a barrier which physically separates the adjacent raw peritoneal surfaces. However poor results were noted in the presence of blood and probably also at coexisting infections [44]. ORC is not widely used in general surgery today.

The experimental effects of a glucose polymer have been promising, reducing adhesions without obvious side effects [45,46]. In a RCT it was shown that this polymer reduces the incidence of adhesions and that its application is safe and easy [46]. However, a Meta-analysis report on pelvic adhesion, has not recommended this polymer for the prevention of intra-abdominal adhesions [47].

Hyaluronic acid (HA) is a naturally occurring glycosamin which is biocompatible, non immunogenic and bioabsorbable, therefore it seems to be well suited as an anti-adhesive agent [48]. Compounds consisting of HA act as a barrier because they coat serosal surfaces and provide a certain degree of protection from serosal desiccation and other types of injury. But they have also been shown to have an anti-inflammatory effect [49-51]. The most popular product on the market is Seprafilm^®^, a combination of HA and CMC. Seprafilm^® ^reduces adhesive formation, but it is very expensive [13]. Its use increases the risk of anastomotic deshiscence, the formation of abscess [23] and inflammatory reaction [52].

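### Under the general safety-population rule, the anastomotic leakage rate and its 90% interval would include patients without an anastomosis, so absolute leak risk is diluted by an unstated factor

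*Protocol article*

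**What the plan says.** - **Endpoint.** Secondary endpoints: "Occurrence of anastomosis leakage within 28 (+10) days after surgery". Table 1 gives diagnostic criteria for leakage but does not say who counts as at risk.
- **Importance.** Objectives of the study compares adverse events between the groups as further evidence on safety, "with special attention to anastomotic leakage".
- **Analysis set.** Statistical consideration and sample size estimation: "The safety analyses will be conducted in the safety population, including all randomized patients with group assignment by treatment received". No exception is stated.
- **Summary.** The same section says that "adhesion and complication rates will be calculated with two-sided 90% confidence intervals". It describes a confidence interval for a difference between arms only for the primary endpoint.
- **Eligibility.** The procedural criterion in Table 2 is "Patients of both sexes undergoing a primary elective median abdominal incision", with an expected incision of at least 15 cm. No inclusion or exclusion criterion concerns an anastomosis.
- **Allocation.** Randomization describes 1:1 allocation in blocks of varying size, before the abdominal wall is closed. It mentions no stratification by anastomosis.
- **Window.** The abstract has "The frequency of anastomotic leakage within 28 days after operation", without the 10-day extension that it gives the primary endpoint one sentence earlier.

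**The concern.** Only a patient with an anastomosis can have an anastomotic leak. The article treats leakage as a safety item, fixes all randomised patients as the safety population and admits patients with or without an anastomosis. Together these put patients with zero risk into the denominator.

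The article itself explains why this harm matters. Of a hyaluronic acid and carboxymethylcellulose film, the Discussion says "Its use increases the risk of anastomotic deshiscence". It also describes a trial of a hyaluronic-based gel that was stopped early because of adverse effects, including a high incidence of anastomotic dehiscence. In a first-in-man safety study, a surgeon planning to use the gel after bowel resection needs the leak risk in patients who have an anastomosis. A rate over all patients understates that risk whenever some have none. The reassurance is most misleading when few or no leaks occur.

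**Working it through.** **1. The plan's own figure.** The article gives no figure for leakage. Its only power statement concerns the primary endpoint: with 30 per arm, one-sided 5%, 80% power and a control rate of 10-15%, a difference of 20-25 points can be excluded. Using margin = (1.645 + 0.842) × √(2p(1−p)/30):

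- p = 0.10: 19.3 points
- p = 0.15: 22.9 points

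The stated range is reproduced, and nothing below touches it.

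**2. Dilution.** Let f be the share of patients with an anastomosis, and p_T and p_C the leak risks among them in the gel and control arms. Over all patients the risks are f·p_T and f·p_C, and the risk difference is f·(p_T − p_C).

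**3. Illustration.** The article gives neither f nor a leak rate. Assumed here: p_C = 5% and p_T = 20%, a difference of 15 points, with 30 per arm and 30f at risk per arm. The upper 90% limit is the difference + 1.645 × SE, evaluated at the expected rates.

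- At risk: SE = √[(0.20·0.80 + 0.05·0.95)/(30f)]
- All patients: SE = √[(f·0.20(1 − f·0.20) + f·0.05(1 − f·0.05))/30]

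| f | At risk per arm | Difference, at risk | Difference, all | Upper 90% limit, at risk | Upper 90% limit, all | z, at risk | z, all |
|---|---|---|---|---|---|---|---|
| 1 | 30 | 0.15 | 0.150 | 0.287 | 0.287 | 1.80 | 1.80 |
| 0.8 | 24 | 0.15 | 0.120 | 0.303 | 0.245 | 1.61 | 1.58 |
| 0.6 | 18 | 0.15 | 0.090 | 0.327 | 0.200 | 1.40 | 1.34 |
| 0.5 | 15 | 0.15 | 0.075 | 0.343 | 0.177 | 1.28 | 1.21 |
| 0.3 | 9 | 0.15 | 0.045 | 0.400 | 0.125 | 0.99 | 0.92 |

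At f = 0.5, for example, the SE is √(0.2075/15) = 0.118 at risk and √(0.114375/30) = 0.062 over all patients.

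As f falls, the at-risk limit rises because there is less information. The all-patient limit falls because more patients cannot leak. The z columns hardly differ, so the effect is on absolute size and not on the test.

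**4. No leaks in an arm.** The exact one-sided 95% upper limit, which is also the upper end of the two-sided 90% interval, is 1 − 0.05^(1/n):

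- 30 patients: 9.5%
- 24 patients: 11.7%
- 18 patients: 15.3%
- 15 patients: 18.1%
- 9 patients: 28.3%

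**5. A few leaks in an arm.** With f = 0.5 assumed, 3 leaks among 15 at risk is 20.0% (exact 90% interval 5.7-44.0%). The same leaks over 30 patients give 10.0% (2.8-23.9%).

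**6. Chance differences in the share.** With f = 0.5 and independent binomial counts, the difference in share between arms has SD √(2·0.25/30) = 0.129, and 1.96 × 0.129 = 0.253. The arms differ by 5 or more anastomosis patients in about 25% of such randomisations (20% at f = 0.7).

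**The case against.** **The denominator is inferred.** No sentence about leakage fixes it. The statistical section defines an analysis set, and an at-risk rate computed within that set would not breach it. For adhesions, the article already records assessment points as well as patients. An analysis plan that is not shown could add an at-risk subset. This stands in part: the point must be put as what follows from a general rule. But that rule carries no exception, and a reader applying it would use all patients.

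**The size is assumed.** This stands. The article gives no f, and at f = 1 the problem disappears.

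**The comparison is sound anyway.** This also stands. A reader might infer that chance imbalance in the anastomosis share biases the all-patient comparison. It does not: randomisation keeps that comparison unbiased for the population treated, the test statistic barely moves, and a risk ratio is not diluted on average. Nor does the table show a failed safety criterion. The 0.25 limit belongs to the primary endpoint, and leakage has no margin or hypothesis.

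**The class signal is indirect.** The products with reported dehiscence are based on hyaluronic acid, one of them combined with carboxymethylcellulose. This gel is polyvinyl alcohol with carboxymethylcellulose, and the Discussion reports no impairment of anastomotic healing in animals. So the documents do not support calling leakage an established harm of this gel. The article's own promise of special attention is enough to justify a usable leak rate.

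**The subset may not be fixed before randomisation.** Design says only that randomisation takes place during the operation. Randomization places it before wall closure, and Intervention has the gel applied after the surgical procedure. That the anastomosis always comes first is plausible but not stated, so the subset definition should say so.

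**Conclusion.** The point holds in a limited form. Under the article's general safety rule and Table 2, the leak rate and its 90% interval would cover patients without an anastomosis. Absolute rates and risk differences then shrink by f, with an interval that looks too tight for the patients at risk. Under the assumed 5% and 20% leak risks, 15 points becomes between 4.5 and 12 points for f from 0.3 to 0.8. With no leaks in an arm and f = 0.5, the upper limit reads 9.5% where the at-risk data support only 18.1%.

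This is a matter of reporting the right quantity. It does not make the randomised comparison invalid, and it leaves the primary endpoint and its power statement untouched. The difference between 28 days in the abstract and 28 (+10) days in the body is a separate, minor inconsistency that adds nothing to the denominator argument.

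**What to change.** State that leakage is reported by arm, and as a difference with its two-sided 90% confidence interval, among patients in whom an anastomosis was made before randomisation. An anastomosis made before allocation is a baseline characteristic, so this subset keeps the randomised comparison. Group the patients by treatment received, as for the other safety analyses. Give the number and share with an anastomosis in each arm, and keep the all-patient rate as supportive. Align the abstract's window with the 28 (+10) days under Secondary endpoints.

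The cost is a few lines of text and a wider interval from fewer patients. Recruitment is already complete, so the subset would have to be identified from operative records. If outcomes by arm have been seen by the time it is defined, the report should say so.

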### Design

This is a prospective, randomised, controlled, double-blinded, single centre study. Patients will be blinded as well as the evaluating physician conducting the ultrasound examination. In case of a non sufficient recruitment this study can be expanded into a multicentre trial. Patients enrolled in the trial will be randomly allocated either to the treatment group receiving A-Part^® ^Gel or to the untreated control group (for inclusion and exclusion criteria see table 2). Randomisation will take place during the operation. Initially there will be a staggering of the treatment of the patients, so that during the early phase of the study there is a one-by one exposure of patients to A-Part^® ^Gel. Both groups consist of 30 patients. After discharge from the hospital the investigator will examine the patients at 28 days (+10) and after 3 months (±14 days) after surgery (figure 1).

**Table 2 T2:** Eligibility Criteria

Inclusion criteria	Exclusion criteria
• Patients of both sexes undergoing a primary elective median abdominal incision	• Patients with a known history of adhesion or peritonitis
• Age equal or greater than 18 years	• Patients with a known sensitivity to polyvinylalcohol or carboxy-methylcellulose
• Written informed consent	• Simultaneous participation in another clinical trial with interfering end-points
• Expected incison length ≥15 cm	• Emergency surgery
• Expected survival time more than 12 months	• Patients with peritoneal carcinosis or peritoneal dialysis
• For female adults of reproductive potential: negative pregnancy test at visit 1 and sufficient contraception from time of written consent up to at least 4 months	• Patients with systemic immunsuppression (e.g. hydrocortisone >50 mg per daily, other immunsuppressants like Azathropin, Mycophenolatmofetil, Ciclosporin, Everolimus, Methotrexat ect.), chemotherapy or radiotherapy within the last 2 weeks prior surgery
	• Patients with ascites >200 ml
	• ASA > 3
	• Patients with intra-abdominal abscess or other intra-abdominal infection
	• Renal impairment (Creatinine >1.3 mg/ml)
	• Pregnant or breast-feeding women
	• Lack of compliance
	• Surgical procedures or patients which require insertion more than 2 intra abdominal drains

